### Additional outcomes

The following clinical outcomes will be collected retrospectively for all three phases: Blood creatinine, BUN level, acute and chronic rejection, infection, health-related quality of life and death from the medical record and from primary data collection. Acute and chronic rejection episodes will include those that are biopsy-proven and/or medically treated (3-day dose of intravenous prednisone) as such. Infection episodes will include those in which the blood, sputum, and/or urine culture is positive for an abnormal organism. Deaths will be reported from the transplant team.

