### Statistical analysis

Sample size and power calculations are based on comparing expected change in medication adherence rate of patients in each group at six months - an expected adherence mean difference of 10 % based on our pilot study findings and the literature. We use an alpha of .05 and provide for 90 % power to detect indicated effect sizes in this two-arm randomized study. An effect size difference of 70 % is based on a conservative estimate of our pilot work. A sample size of 46 older KT recipients per group (final total sample 92) will meet these assumptions and provide sufficient power. Recruitment and retention rates are calculated from our pilot study, other adherence studies at the same sites, and are documented in one similar RCT adherence study in older KT recipients [63, 64]. We selected an adherence rate of 85 % to divide the adherers from the non-adherers based upon our preliminary work describing 4 clusters of KT medication adherers: those who (1) take medications on time (1.0-.85 MA rate), (2) take medications on time with late/missed doses (.84-.70 MA rate), (3) rarely take medications on time and who were late with morning and/or evening doses (.69-.20 MA rate), and (4) missed many doses (<.20). Even minor deviations in dosing adherence lead to poor outcomes, though no studies have determined the criterion adherence “dose” that distinguishes good and poor outcomes.

Appropriate descriptive analyses will be performed to examine distributional characteristics for collected measures, as well as to summarize changes over time as a function of group assignment. During this initial phase, we will explore bivariate relationships among primary and secondary outcome measures and variables thought to affect medication adherence. In addition, we will conduct analyses to determine whether the randomly assigned groups are equivalent at the start of the study on the demographic and other measures collected at baseline. Before hypothesis-testing analyses are conducted, exploratory analyses will be performed to examine the effect of various mediators and moderators on the relationship between intervention, adherence, and clinical outcome. The results of these analyses will determine what additional variables will be incorporated in the subsequent hypothesis testing (e.g., analysis of covariance).

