Our primary analysis assesses whether the SystemCHANGE™ intervention is more effective than the attention-control intervention in increasing MA in adult kidney transplant recipients at the completion of the 6-month intervention and 6-month maintenance phases. We hypothesize that adult kidney transplant recipients receiving the SystemCHANGE™ intervention will have higher immunosuppressive MA rates than the attention-control group at the completion of intervention and maintenance phases. Since rate responses will most likely violate the normality assumption, the non-parametric method, Mann- Whitney test, will be used for comparing the two groups. However if the normal assumption is satisfied through transformation or as raw data measures, t-test will be applied for group comparison. Possible covariates resulting from demographic data and screening phase MA will be included in the analysis to adjust for possible bias.

Our secondary analysis assesses the MA patterns in both the SystemCHANGE™ and attention-control groups. Specifically we are interested in determining when the intervention becomes effective (e.g., what “dose” is needed) and the pattern of decay in MA over time in both groups. The dependent variable for these research questions are the repeated measurements of immunosuppressive MA rates at 12 time points [i.e. 1, 2, 3, 4, 5, 6, 7, 8, 9, 10, 11 and 12 months] and the independent variable is group assignment and time effect. Poisson regression analysis will be used for these questions. Proc Nlmixed procedure in SAS will be used for Poisson regression modeling. In order to answer the hypothesis we will test for group-by-time interaction to test if the two groups have different time profiles for MA or not. Possible covariates resulting from demographic data and screening phase MA will be included in the model to adjust for possible bias. Repeated measures from the same Pp will be accounted for using a random effect in the model.

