Our exploratory analyses focuses on three aims: 1) to determine whether the SystemCHANGE™ intervention is more effective than the attention-control intervention in decreasing poor health outcomes (e.g. increasing creatinine/BUN, infection, acute/chronic rejection, graft loss, death), 2) to evaluate the role of potential mediators (social support, and systems-thinking) and moderators (ethnicity perceived health and level of medication nonadherence) of MA and health outcomes in adult kidney transplant recipients receiving the SystemCHANGE™ intervention, and 3) to determine if the SystemCHANGE™ intervention is cost-effective.

We expect to observe lower levels of poor health outcomes in the SystemCHANGE™ group as compared to the control group. The dependent variables are the dichotomous outcomes such as, infection, acute and chronic rejection, graft loss, and death and numeric outcomes such as creatinine, and BUN.

The independent variable is group assignment. Chi-square tests will be applied to estimate and test the relationships between dichotomous outcome variables and the independent variable. For continuous outcomes variables t test or Mann-Whitney test will be conducted to test for group effect depending on the satisfaction of normality assumption.

Our secondary exploratory aim is to evaluate the role of potential mediators and moderators of MA and health outcomes in adult kidney transplant recipients receiving the SystemCHANGE™ intervention and recipients receiving the attention-control intervention. We hypothesize that exploring potential mediators and moderators in the analyses will enhance the interpretation of treatment effect on MA. To test for mediator effect, the dependent variable is MA and the independent variable is treatment group. Potential mediators are social support and systems thinking. Poisson regression will be applied to estimate the mediator effect [65] and the Sobel test [66] will be used to test if the mediator effect is significant. Changes in the variance with mediator in the models will be estimated and reported as part of the analysis results. To test for moderator effect, the dependent variable is MA and the independent variable is treatment group. Potential mediators are ethnicity group, perceived health and MA level (different strata). Poisson regression will be applied to estimate and test for possible moderator effect through interaction terms between the independent variable and moderator [65].

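### Creatinine and BUN are to be compared by a two-group test that does not use the screening values the trial collects, giving up efficiency at no saving

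*Protocol article*

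**What the plan says.** In the Statistical analysis section, under the exploratory analyses, the dependent variables include "numeric outcomes such as creatinine, and BUN". The text then says "The independent variable is group assignment" and gives the test: "For continuous outcomes variables t test or Mann-Whitney test will be conducted to test for group effect depending on the satisfaction of normality assumption".

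The section on Additional outcomes says "The following clinical outcomes will be collected retrospectively for all three phases: Blood creatinine, BUN level", and Table 2 ticks both variables for screening, intervention and maintenance.

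Two other statements in the Statistical analysis section concern covariates.

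- For the primary MA comparison: "Possible covariates resulting from demographic data and screening phase MA will be included in the analysis to adjust for possible bias". An equivalent commitment is made for the repeated-measures MA model, but none for creatinine or BUN.
- Before that, after describing exploratory work on mediators and moderators: "The results of these analyses will determine what additional variables will be incorporated in the subsequent hypothesis testing (e.g., analysis of covariance".

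The hypothesis on poor outcomes, in the Aims, is set at 12 months.

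**The concern.** Recipients are eligible whatever the time since transplant, and re-transplants are included (Eligibility and exclusions). Graft function can therefore be expected to differ between participants for reasons that predate randomisation and persist through follow-up. A comparison of follow-up values with group as the only explanatory variable leaves those stable differences in the error term. The design does not balance them either, because randomisation is stratified by adherence level only.

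The plan adjusts for the screening value of MA but not for the screening values of creatinine and BUN, which are equally available. At stake is the precision of the group comparison on graft function in a trial of about 92 participants.

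**Working it through.** **Sample size.** The article gives 46 per group with these inputs: "We use an alpha of .05 and provide for 90 % power to detect indicated effect sizes in this two-arm randomized study" and "An effect size difference of 70 % is based on a conservative estimate of our pilot work". Read the effect size as d = 0.70 and alpha as two-sided (sidedness is not stated).

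- Normal approximation: n = 2 × ((1.960 + 1.282)/0.70)² = 42.9 per group.
- Exact t-test: 43.9 per group.
- Divided by the Mann-Whitney efficiency 3/π: 43.9 × π/3 = 45.9, so 46.

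The stated figure reproduces. It concerns MA only. The article gives no SD, target difference or correlation for creatinine or BUN. The figure is used below only to fix 46 per arm.

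**Variance of the group comparison.** Let ρ be the correlation between screening and follow-up values, and assume equal variances at the two times. Relative to an unadjusted comparison of final levels:

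- final level: 1
- change from screening: 2(1 − ρ)
- ANCOVA on the screening value: 1 − ρ²

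ANCOVA therefore removes a share ρ² of the final-level variance. Against the change score the ratio is (1 − ρ²)/(2(1 − ρ)) = (1 + ρ)/2, which is never above 1.

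**Numbers.** ρ is assumed. The last three columns are for ANCOVA with 46 per arm and two-sided alpha 0.05. Effective n is 46/(1 − ρ²). The 0.4 SD difference is illustrative and does not come from the documents.

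| ρ | Change factor | ANCOVA factor | Variance removed vs final level | Effective n per arm | Detectable difference, 80% power | Power for 0.4 SD |
|---|---|---|---|---|---|---|
| Unadjusted final level | – | – | – | 46 | 0.59 SD | 47.5% |
| 0.5 | 1.00 | 0.75 | 25% | 61 | 0.51 SD | 59% |
| 0.7 | 0.60 | 0.51 | 49% | 90 | 0.42 SD | 76% |
| 0.8 | 0.40 | 0.36 | 64% | 128 | 0.35 SD | 89% |
| 0.9 | 0.20 | 0.19 | 81% | 242 | 0.26 SD | 99% |

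**If change is what is tested.** At ρ = 0.8 the factor goes from 0.40 to 0.36, a reduction of 10%. At ρ = 0.5 it goes from 1.00 to 0.75. Below ρ = 0.5 the change score has a larger variance than the unadjusted final level.

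**When more than half the variance is lost.** ρ² > 0.5 requires ρ > 0.707.

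**Chance imbalance.** With 46 per arm, the screening means differ with standard error √(2/46) = 0.21 SD. A difference beyond 0.2 SD either way (0.2/0.21, about 0.96 standard errors) arises in about one trial in three. A share ρ of it carries into an unadjusted final-level comparison. This is the same variance seen another way, not an additional loss.

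**The case against.** The strongest reply has four parts.

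1. **The plan does not say that final levels are compared.** The aim refers to rising creatinine and BUN, which could mean change, and a test of change already uses the screening value. The expectation of lower levels points the other way. The text is ambiguous, so the objection stands as a limit on the size of the loss. It does not remove the point, because ANCOVA is at least as efficient on either reading.

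2. **Covariance analysis is mentioned.** That is so, and the door to adjustment is not fully closed. But the variables are to be chosen from exploratory results, the listed mediators and moderators do not include screening creatinine or BUN, and a Mann-Whitney test takes no covariate.

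3. **The outcomes are exploratory and no power is claimed for them.** This stands. Table 2 lists them as secondary, but the Aims and the analysis text treat them as exploratory. A reader might infer that the unadjusted test is biased or invalid. It is not: in a randomised comparison, chance imbalance is already allowed for in its error rate.

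4. **A journal article leaves covariate lists to the analysis plan.** Often true, and silence would be no finding. Here, though, the article states a specific test and a single independent variable for these outcomes.

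A reader might also infer that most of the available precision is thrown away. That needs ρ above about 0.71. Such a value is plausible for stable graft function, but the documents give no correlation.

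**Conclusion.** The concern holds in limited form. The stated test for creatinine and BUN makes no named use of screening values that are collected anyway. Against a final-level comparison the loss is ρ² of the variance, which is 25% to 81% over the assumed range of 0.5 to 0.9. Against a change score it is smaller, about 10% at ρ = 0.8. These sizes rest on assumed correlations and, for the change score, on equal variances at the two times. The power figures also rest on an illustrative effect, so they do not show that the trial would miss a difference in graft function.

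The consequence is lost efficiency in exploratory outcomes. The type I error rate, the validity of the comparison and the primary MA conclusion are not affected.

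**What to change.** State for creatinine and BUN that the groups will be compared at 12 months, the time point of the stated hypothesis, by ANCOVA. Use the log scale if the values are skewed. Name as covariates the screening-phase value of the same variable and the randomisation stratum (<70% or 70–84% adherence). Report the adjusted difference, or the adjusted ratio on the log scale, with a 95% confidence interval. Keep the unadjusted t-test or Mann-Whitney test as a sensitivity analysis, and say whether it is applied to the level or to the change.

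The cost is a change of analysis wording. No new data, visits or participants are needed, because screening values are already to be collected.

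### The Sobel test, the only significance test named for mediation, gives up roughly 10–20 points of power at 46 per arm for medium paths; a percentile bootstrap interval recovers this at almost no cost

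*Protocol article*

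**What the plan says.** All references are to the Statistical analysis section of the protocol article unless another section is named.

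- **Aim and status.** The aim is exploratory: "Our secondary exploratory aim is to evaluate the role of potential mediators and moderators of MA and health outcomes".
- **Mediators.** There are two: "Potential mediators are social support and systems thinking".
- **Estimation.** "Poisson regression will be applied to estimate the mediator effect".
- **Test.** "the Sobel test [66] will be used to test if the mediator effect is significant". No resampling interval or joint-significance test is mentioned. The next sentence adds a descriptive output: how the variance changes when the mediator enters the model.
- **Sample size.** "A sample size of 46 older KT recipients per group (final total sample 92) will meet these assumptions". The basis is the six-month adherence difference: "We use an alpha of .05", with "90 % power to detect indicated effect sizes in this two-arm randomized study", and "An effect size difference of 70 % is based on a conservative estimate of our pilot work". The article gives no path sizes for the mediators and makes no claim of power for mediation.

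**The concern.** An indirect effect is the product of two coefficients: treatment to mediator (a) and mediator to outcome given treatment (b). The Sobel test divides the estimated product by a first-order standard error and refers the ratio to the normal distribution. With modest samples the product is skewed, so the test tends to reject less often than its nominal level under the null and loses power under the alternative. A bootstrap interval for the same product uses the same data and does not assume normality.

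What is at stake is the mechanism. Social support and systems thinking are the routes through which the trial proposes to explain any effect on adherence. A test that is less sensitive than it need be makes a non-significant result on either mediator harder to interpret. Because the article fixes the test by name, this is a comment on a stated choice and not on a detail left to a fuller document.

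**Working it through.** **1. The plan's own figure.** I read the 70% effect size as a standardised difference of 0.70 and the alpha of .05 as two-sided.

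- Normal approximation: n per group = 2(1.960 + 1.282)² / 0.70² = 42.9, so 43.
- t-test: 43.87, so 44.
- Divided by the Mann-Whitney efficiency of 0.955: 43.87 / 0.955 = 45.94, so 46.

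The stated 46 per group reproduces for the primary comparison. It says nothing about mediation.

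**2. Set-up for the mediation check.**

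- From the article: 46 per arm, alpha .05, Sobel test.
- Assumed, because the article gives no values: a from 0 to 1.4 SD, b from 0 to 0.59 SD per SD, a direct effect of 0.3 SD, and linear models with normal errors for mediator and outcome.
- Sobel statistic: z = ab / √(a²·SE_b² + b²·SE_a²), significant if |z| > 1.96.
- Comparators: a percentile bootstrap 95% interval for ab, and joint significance (a and b each significant).
- Replicates: 10,000 for Sobel and joint significance; 1,500 with 1,000 resamples for the bootstrap. The largest Monte Carlo standard error for the bootstrap column is √(0.25/1500) = 1.3 points.

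**3. Power.** Differences are taken from the rounded percentages.

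| a | b | Sobel | Percentile bootstrap | Joint significance | Bootstrap minus Sobel |
|---|---|---|---|---|---|
| 0.5 | 0.26 | 23% | 45% | 45% | 22 |
| 0.5 | 0.39 | 47% | 64% | 63% | 17 |
| 0.7 | 0.26 | 43% | 61% | 62% | 18 |
| 0.7 | 0.39 | 75% | 88% | 87% | 13 |
| 1.0 | 0.26 | 61% | 70% | 68% | 9 |
| 1.0 | 0.39 | 92% | 95% | 95% | 3 |

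Before rounding, the last difference is 94.5 − 92.2 = 2.3 points. Separate simulations at neighbouring paths agree: at 0.5/0.3, 28% v 50% and 31% v 53% (22 points each); at 0.7/0.35, 69% v 83% (14) and 66% v 81% (15).

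At the extremes the choice of test matters less. For a = 0.3 and b = 0.14, Sobel has 1.5% and joint significance 7%. Across a = 0.3 with b from 0.14 to 0.59, joint significance reaches only 7 to 30%. For a = 1.4 and b = 0.26, Sobel has 65% and joint significance 68%.

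**4. Rejection under the null.**

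- One path zero: Sobel 0.2 to 4.1%, depending on the other path; joint significance 1.4 to 5.1%; percentile bootstrap about 2 to 4% in the settings run.
- Both paths zero: Sobel 0.02%, joint significance 0.2%, percentile bootstrap 0.3%.

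In these settings the bootstrap gains power without exceeding about 5%.

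**5. How far the linear model carries over.** The article plans Poisson regression. I checked a Poisson outcome model with model-based standard errors, assuming mean adherence of 0.70 and an SD of 0.10/0.70 = 0.143. The Sobel result then depends on how adherence is scaled.

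- As a 0–1 rate: power 0% at both 0.5/0.3 and 0.7/0.35.
- As a 30-day score: power 26% and 63%.
- As a 180-day score: rejection of about 24% with the mediator path at zero, so the test is no longer conservative.

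The cause is that the Poisson standard error is right only when variance equals mean. The percentile interval does not use that standard error. The percentages in step 3 are therefore indicative and are not predictions for this trial.

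**The case against.** A reader might infer that the Sobel test is far too conservative here, that real mediators are likely to be missed, or that a moderate indirect effect would usually be reported as absent. The article does not support those statements, for these reasons.

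- **Path sizes are assumed.** At 0.7/0.39 Sobel has 75% power and at 1.0/0.39 it has 92%, so such mediators would usually be found. A larger path is plausible for systems thinking: the intervention targets it, and the Potential moderators and mediators section says the scale separated people with different amounts of SystemCHANGE training.
- **Sample size explains much of the low power.** At 0.5/0.26 the bootstrap also misses more than half of true effects (45% power). The 92 participants were never meant to power mediation.
- **Very low null rejection is not peculiar to Sobel.** With both paths zero, every method rejects far below 5%.
- **A non-significant Sobel result is not the whole report.** The change in variance is to be reported as well.
- **The aim is exploratory.** In the linear settings the test is conservative, so it does not manufacture mediators, and the primary comparison does not depend on it.

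All of this stands, and it limits the size of the point. What remains is that the plan fixes one test, and another using the same data does better across the middle range of paths. The Poisson objection weakens the exact percentages but does not favour Sobel, since its behaviour then depends on the scaling of adherence.

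**Conclusion.** The point holds as a free improvement and not as an error in the plan. With 46 per arm and linear models, the Sobel test costs roughly 10 to 20 points of power against a percentile bootstrap when treatment moves the mediator by 0.5 to 0.7 SD and the mediator-to-adherence path is about 0.26 to 0.39. The loss is about 3 to 9 points at 1.0 SD. Small mediators are beyond reach at this sample size whichever test is used.

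The size rests on assumed path values, a two-sided alpha, all 92 participants being analysed, and linear in place of Poisson models. The article describes the mediator aim once for SystemCHANGE recipients only and once for both arms; if fewer than 92 are analysed, power falls for every method.

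**What to change.** Replace the Sobel test with a percentile bootstrap 95% confidence interval for the indirect effect (for example 5000 resamples, drawing participants within arm), and report the estimate with its interval for each mediator. Adjust for screening-phase adherence. Adjust for the mediator's pre-intervention value only if one is collected: Table 2 ticks social support and personal systems thinking under intervention and maintenance but not under screening, so a baseline value may not exist. Keep the analysis labelled exploratory.

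The cost is a change of wording and computing time. No extra participants, visits or data are needed.

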## Design

This is a 4-year, two-center, randomized controlled trial, that is single-blind (participants [Pps]) and uses a stratified sample block design with repeated measures. We are comparing the SystemCHANGE™ intervention to the attention control intervention in adult kidney transplant recipients with existing medication nonadherence documented by electronic monitoring. The repeated-measures design provides longitudinal data regarding medication nonadherence which allows us to determine when the intervention becomes effective (to determine if a lower dose of SystemCHANGE™, e.g. shorter time of delivery, is possible). It also allows us to track possible decay in medication nonadherence over time following the intervention.

We are examining the experimental effect on the outcome variable MA. During the 3-month screening phase, all Pps are using electronic monitoring to document medication taking. Those who are adherent (MA rate of .85 % or greater) exit the study. To prevent the “ceiling” effect, those with documented medication nonadherence (MA rate of less than .85 %) are stratified by low (<70 %), and moderate (70-84 %) nonadherence, based upon our previous medication nonadherence pattern research [41]. They then enter the intervention phase of the study and are randomized into either the treatment (SystemCHANGE™ intervention) or the attention control group (attention control condition). During the 6-month intervention phase, all Pps receive a home visit at baseline plus six telephone calls (at intervention months 1, 2, 3, 4, 5, 6). In addition, Pps randomized into the SystemCHANGE™ intervention are also guided in implementing SystemCHANGE™ activities related to medication taking by the Research Assistant (RA). Control group Pps receive RA-provided education guided by healthy living patient educational materials. The maintenance phase begins after the intervention and runs for an additional 6 months. This phase examines how Pps maintain MA in the absence of an intervention; however, we are continuing to use electronic monitoring to measure the outcome variable. Health outcome and healthcare cost data are collected during the intervention and maintenance phases.

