### Primary outcome - medication adherence

Table 2 provides an overview of study measures and outcomes. The MA calculation method has been previously described but will be briefly described here [41]. A 0.5 is assigned if the dose of the immunosuppressive medication is taken within a 3-hour window (+/-1.5 hours of the prescribed time); 0.25 is assigned if the dose of the immunosuppressive medication is not within the 3-hour window but is taken within a 12-hour window (+/-6 hours of the prescribed time), and 0 is assigned if the dose of the immunosuppressive medication is not taken within a 12-hour window (+/-6 hours of the prescribed time, i.e., if the dose was missed). On each day, an individual is assigned a score of 0, 0.25, 0.50, 0.75 or 1 points (p. 526).

**Table 2 Tab2:** Study outcomes and measures

	Screening	Intervention	Maintenance
*Inclusion Criteria*			
6-item telephone measure of cognition	√		
Primary Outcome			
Medication adherence–electronic medication monitoring	√	√	√
Secondary Outcomes			
Creatinine	√	√	√
Blood urea nitrogen	√	√	√
Acute rejection	√	√	√
Chronic rejection	√	√	√
Infection	√	√	√
Death	√	√	√
*Potential Mediators*			
Social Support		√	√
Perceived Health		√	√
Personal Systems Thinking		√	√
*Background*/*Moderating Variables*			
Medical History	√		
Demographics (ethnicity)	√		
Level of Medication Nonadherence	√		
Pillbox use	√		
*Health care costs*			
Hospitalizations, clinic, observation, and ER visits	√	√	√

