### Cost-effectiveness

The primary endpoint of cost-effectiveness measures will be the incremental cost-effectiveness ratio (ICER) of the SystemCHANGE™ intervention relative to the attention-control, which assesses the incremental cost per health-related quality-adjusted life year gained. The perspective of cost-effectiveness is a third-party payer. A micro-costing approach will be used to measure the intervention’s resource use, based on a log of resource use for each intervention. The resources used for the delivery intervention in the interventional and the control group will be tracked over the study period. The Pps will track the type and quantity of medical services consumed (doctor’s office, clinic, hospital, medication). The unit cost of personnel time will be based on actual hourly salary rates and fringe benefits. Unit costs of each hospitalization, ER visit, clinic visit, and physician fee will be estimated based on Medicare’s average reimbursement rate. The unit cost of medication will be estimated from the average wholesale price plus the dispensation fee of 2 %. To determine the number of quality-adjusted life years over the observational period, the weight will be multiplied by the number of days in the observational period. All cost measures will be adjusted to the constant U.S. dollar. Sensitivity analyses will examine key parameters that may affect ICERs.

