Our third exploratory aim is to determine if the SystemCHANGE™ intervention is cost-effective. Our hypothesis is the cost for the SystemCHANGE™ intervention will be less than the cost for the attention-control intervention. To determine the cost-effectiveness of the SystemCHANGE™ intervention compared to the attention-control intervention, both intervention and resource use costs will be evaluated and compared to MA change. A cost-effectiveness analysis will be performed at the end of the intervention period and again at the end of the maintenance period. If there is no treatment effect, a cost-analysis will not be performed. The analysis performed at the end of the maintenance period will be cumulative, incorporating costs and benefits incurred throughout the project. A cost-effectiveness analysis, performed at the end of the maintenance period (calculated for both the intervention and maintenance periods), will evaluate both intervention and control, and resource use costs which will be compared to adherence change. The sum of the total intervention and control costs and resource use costs will be the numerators for testing this hypothesis. The change in adherence (from baseline to end of intervention [or end of maintenance] period) will be the denominator. We will identify all direct intervention costs related to the intervention and the control (planning, designing, and implementation of each intervention, personnel, supplies, travel, and equipment). We will identify resource use costs (hospitalizations, clinic, observation, and ER visits) for both groups. Resource use costs will be obtained from publically available data, e.g. Hospital Compare, Hospital Stats, H-CUP. The DRG will be obtained with a conversion rate and then adjusted by hospital specific information, e.g. academic, location.

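### The cost comparison gives no role to the screening-phase resource use that Table 2 schedules, which gives up some precision but causes no bias

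*Protocol article*

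**What the plan says.** The cost analysis is exploratory: "Our third exploratory aim is to determine if the SystemCHANGE™ intervention is cost-effective". Its cost term is defined in the Statistical analysis section: "The sum of the total intervention and control costs and resource use costs will be the numerators for testing this hypothesis". The effect term is defined relative to baseline: "The change in adherence (from baseline to end of intervention [or end of maintenance] period) will be the denominator".

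On the period covered, the same paragraph first calls the final analysis cumulative over the whole project. It then describes it as "performed at the end of the maintenance period (calculated for both the intervention and maintenance periods").

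On what is collected, the health care costs row of Table 2 ("Hospitalizations, clinic, observation, and ER visits") is ticked for screening, intervention and maintenance. The Design section states a shorter window: "Health outcome and healthcare cost data are collected during the intervention and maintenance phases".

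For the primary adherence analysis the plan names a baseline covariate: "Possible covariates resulting from demographic data and screening phase MA will be included in the analysis to adjust for possible bias". The secondary adherence model has a matching sentence. The cost paragraph has none. The Cost-effectiveness section adds only this on uncertainty: "Sensitivity analyses will examine key parameters that may affect ICERs".

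**The concern.** Health-care costs are skewed, and past use tends to predict later use in the same person. Nothing in the design balances prior use. Randomisation is stratified on adherence level, and recipients at any time since transplant, including those with a re-transplant, are eligible. With 46 per arm, a few heavy users can fall into one arm by chance. A pre-randomisation measure that would absorb part of this is already in Table 2, but the cost analysis does not use it.

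Two wording problems make this harder to settle. The Design section and Table 2 differ on whether costs are collected in screening at all. The cumulative wording also leaves open whether screening cost belongs inside the total. At stake is the precision of the incremental cost and, when the true difference is small, the stability of its sign.

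**Working it through.** **1. Plan's own figure.** The article gives no figure for cost. The only number used here is 46 per arm, which was set for adherence. It reproduces: with a standardised difference of 0.70, alpha 0.05 (two-sided assumed) and 90 % power, the t-test needs 43.87, so 44 per arm. Dividing by the Mann-Whitney efficiency of 0.955 gives 45.94, so 46.

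**2. Which collection window is likely.** The Design sentence covers health outcomes and costs together and omits screening for both. The Additional outcomes section has clinical outcomes collected for all three phases, and Table 2 agrees for outcomes and costs alike. The Design sentence does not say that collection is confined to the later phases. It is therefore more likely incomplete than a competing schedule, but the text has to be reconciled.

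**3. Precision.** Work in units of the follow-up cost SD, and let ρ be the correlation of screening cost with follow-up cost. The documents give no value for ρ, so a range is shown.

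- Unadjusted SE = √(2/46) = 0.2085.
- Adjusted SE = 0.2085 × √(1 − ρ²).
- Variance inflation from not adjusting = 1/(1 − ρ²).
- Equivalent sample size per arm = 46/(1 − ρ²).
- Carry-over of a one-SE chance imbalance at screening = ρ × 0.2085.

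| ρ | Adjusted SE | Variance inflation | Equivalent n per arm | Carry-over, 1 SE | Carry-over, 1.96 SE |
|---|---|---|---|---|---|
| 0.1 | 0.2075 | 1.01 | 46.5 | 0.02 | 0.04 |
| 0.2 | 0.2043 | 1.04 | 47.9 | 0.04 | 0.08 |
| 0.3 | 0.1989 | 1.10 | 50.5 | 0.06 | 0.12 |
| 0.4 | 0.1911 | 1.19 | 54.8 | 0.08 | 0.16 |
| 0.5 | 0.1806 | 1.33 | 61.3 | 0.10 | 0.20 |
| 0.6 | 0.1668 | 1.56 | 71.9 | 0.13 | 0.25 |

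Estimating the slope costs about 1/(92 − 4) = 1.1 % of variance, so at ρ = 0.1 the gain is nil.

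**4. Check with skewed costs (all cost inputs assumed).**

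- *Event-based costs:* gamma-distributed event rates with mean 1.5 per year, exponential cost per event, 3 months of screening, 12 months of follow-up, 46 per arm, no true difference. Three levels of between-person variation gave ρ of about 0.26, 0.40 and 0.52. Adjustment cut the SE by 3 %, 8 % and 17 %. The mean difference was near zero both with and without adjustment.
- *Log-normal costs:* CV 1.5 for follow-up and 2.0 for screening, 20,000 simulated trials per setting. At ρ = 0.21, 0.29, 0.38 and 0.47, the unadjusted variance exceeded the adjusted by 8 %, 16 %, 28 % and 46 %. The formula gives 5 %, 9 %, 17 % and 28 %. With heavy skew the formula is a guide and can understate the gain.

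**5. Dollar illustration (assumed).** Take a 12-month mean of 30,000 dollars and CV 1.5, so SD 45,000. The SE of the difference is 45,000 × 0.2085 ≈ 9,400. At ρ = 0.38, a one-SE screening imbalance shifts the unadjusted difference by 0.38 × √(2/46) × 45,000 ≈ 3,570 dollars, which is 0.38 of one SE.

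**6. Effect of the window.** If the total covers only post-randomisation periods, carry-over is ρ × imbalance as above. If screening cost is counted in the total, the screening difference also enters directly. It would still be chance and not bias, but it would be avoidable noise.

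**The case against.** The strongest reply is that the article never calls the cost comparison unadjusted. It defines the cost variable and neither names nor excludes a model. A condensed article may leave cost covariates to an analysis plan, and this aim is exploratory. That stands in part: the absence of adjustment is inferred from a sum-and-ratio definition that gives screening cost no role. The general clause allowing covariates after exploratory analyses does not fill the gap, because it concerns mediators and moderators of the link between intervention, adherence and clinical outcome.

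It is also fair that a change-from-baseline denominator defines an effect measure and does not oblige costs to be baseline-referenced. The point does not rest on that contrast.

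A reader might infer that chance differences in prior use pass in full into the cost difference and bias it. The documents do not support this. Allocation is randomised, so the unadjusted contrast is unbiased. With a post-randomisation total, only ρ × imbalance carries over. Adjustment would not rescue a comparison this imprecise either: in the illustration the shift is well inside one SE.

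Finally, the stakes are limited. The cost analysis is skipped if there is no treatment effect, and sensitivity analyses of the ratio are already planned. Those vary parameters, however, and do not address baseline cost.

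**Conclusion.** The point holds as a minor one. A baseline measure that Table 2 schedules is unused in the stated cost comparison, and two passages leave its collection and its place in the total unclear. Nothing here biases the result. The loss is precision, by the factor 1/(1 − ρ²): negligible at ρ = 0.1, about 10 % of variance at 0.3 and 33 % at 0.5, and somewhat more if costs are heavily skewed. Every magnitude rests on an assumed ρ and assumed cost distributions. Three months of infrequent hospital use may predict the following year only weakly, in which case the gain is small.

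**What to change.** 1. Align the Design section with Table 2 on collecting resource use in screening. The covariate is available only if Table 2 is the true schedule.
2. State in the cost-effectiveness paragraph of the Statistical analysis section that the cost total covers only the post-randomisation periods, and remove the wording that could bring screening cost into the sum.
3. Estimate the incremental cost from a regression on arm, screening-phase resource-use cost and randomisation stratum, for example a linear model with bootstrap intervals. Report the unadjusted difference as a sensitivity result.

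The cost is wording only, with no data beyond Table 2. It should be settled before cost data are examined by arm.
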